### 4.2. Secondary outcomes

Objective functional outcome in Knee Injury and Osteoarthritis Outcome Score (KOOS) or HHS scale and WOMAC;Correlation of FINDRISC scale results with cardiovascular events and/or surgical site or implant complications.

### 4.3. Patient-reported outcomes

The KOOS was developed to evaluate short- and long-term symptoms and function in patients with knee injury. It is used for both OA assessment and several other types of knee injury.^[32,34]^ The questionnaire is currently culturally adapted in 39 languages, including a validated polish version.^[34–37]^

The HHS is a widely used and relatively simple multidimensional observational THA assessment.^[38]^ The questionnaire consists of questions about pain and activities of daily living, hip function, and range of motion. It has been used to differentiate the outcome of THA^[39]^ and for evaluating hip arthroscopy in younger patients.^[40]^ There is no polish language adaptation of HHS.

The WOMAC has been developed for knee and/or hip joints OA symptoms assessment. Reliability and validity in measuring changes in patients’ symptoms in affected joints has been extensively tested.^[41,42]^ There is no polish cultural adaptation of WOMAC, therefore WOMAC index will be calculated from KOOS.^[43]^

## 5. Risks

### 5.1. Cardiovascular risk

FINDRISC is widely used as a tool to recognize individuals at high risk of developing type 2 diabetes mellitus (T2DM) within 10 years. It has also been used to identify undiagnosed T2DM, abnormal glucose tolerance and metabolic syndrome.^[44,45]^

The SCORE is used to calculate the 10-year risk of cardiovascular mortality in individuals without preexisting atherosclerotic diseases. It has been designed to evaluate the impact of such risk factors as gender, age, smoking status, lipids, and systolic blood pressure, which significantly affect the overall risk and increase the likelihood of a future CVD event.^[46]^

## 6. Discussion

It is well established that DM in patients undergoing surgery is associated with increased risk for complications and increased length of hospital stay.^[45]^ In general, hyperglycemia is considered to cause abnormalities in the host’s physiologic response to a bacterial load not only in diagnosed with DM patients.^[46]^ Fasting blood glucose of > 140 mg/dL has been associated with a 3-fold increased risk for an infection independently on glucose metabolism.^[47]^

Periprosthetic joint infection remains a devastating complication after THA. Poor patient satisfaction and increased socioeconomic costs are associated with this along with increased mortality.^[48–50]^

Total joint arthroplasty is considered a relatively safe procedure globally for an overall condition, as reported rates of major cardiac complication, mostly attributable to myocardial infarction, are as low as 0.2% to 0.8%.^[51,52]^ However, this risk is prognosed to increase significantly with the predicted increase in number of arthroplasties in the future, therefore the adequate measures to minimize the influence on body metabolism, must be developed.^[53–55]^ Factors associated with cardiac complications are increased hospital mortality, increased length of stay and expenditure, increased number of noncardiac events.^[53,56–60]^

The literature lacks valuable information indisputably designing an evidence-based approach to patients suffering from T2DM in orthopedic surgery departments to decrease prevalence of potentially debilitating adverse events. Since there are currently available only empiric recommendations, there is a need for well-designed studies of preoperative T2DM management, particularly for orthopedic surgeries. This could minimize procedure delays, patients’ dissatisfaction and reduce morbidity and mortality. Hyperglycemia on the day of surgery is a significantly dangerous circumstance for both nondiabetic and T2DM patients, thus there is an urgency of developing the guidelines of proceeding on the patients presenting with this condition.^[61–63]^ The up-to-date database search utilized only a few papers investigating the role of preoperative glycemia on the postoperative outcomes.

A retrospective cohort study conducted by Robin et al aimed to investigate the impact of immediate preoperative capillary glucose levels on complications in a cohort of orthopedic patients admitted to undergo a TKA. This study presented no association between preoperative glycemia measured from capillaries and surgical complications or length of stay.^[64]^

Anderson et al observed that hyperglycemia provokes occurrence of 90-day deep SSI in orthopedic patients. Therefore, the glycemia on an admission may present as an important marker for SSI risk in orthopedics^[65]^ Arteaga et al found that the corrosion behavior on the implemented component of the knee joint prosthesis was not significantly different between diabetic and nondiabetic conditions of immersed disks or implant type. However, poor glycemic control facilitated aluminum release, which further elucidates implant failures. Those findings represent the hallmark of T2DM effects on SSI and implant colonization. Firstly, it is important to associate the presence of hyperglycemia with possibly increased risks and secondarily the design of specific surfaces should be considered. The induction of constructive regimen and healing responses in immunocompromised patients could enhance the outcomes in the risk group. Another finding included exhibition of 10% higher infection rates among T2DM patients than nondiabetic patients. This contributes to lack of efficiency in osseointegration and the issues on the molecular level at the implant–tissue adaptation.^[66]^

The heterogeneity of existing papers concerning the topic of T2DM complications in orthopedic surgery and a small abundance of research done underlines the priority to investigate the topic extensively. DM may paradoxically enhance hypoglycemic events, due to its difficult control in perioperative period. Roche et al demonstrate that the risk for revision TKA due to infection increases as glucose levels decline from the normal range. Preoperative fasting and antidiabetic medications may predispose patients to hypoglycemia.^[67]^ Because of this, several authors have advocated that scheduled surgeries should be performed during morning hours for diabetic patients.^[68–71]^ Prevention of both hyperglycemia and also hypoglycemia is important, as it has been associated with increased hospital costs, length of stay, greater amount of falls and higher mortality, poor outcomes, and more complications.^[67,70]^ The evaluation of their glycemic profile among the hospital stay is needed in order to establish a special protocol for treatment regimen in an effort to optimize the overall condition. And it remains an undiscovered topic. Since orthopedic surgery utilizes the general anesthesia, but afterwards patients are allowed to take a standing position rapidly, the proper control of blood glucose fluctuations are crucial in order to prevent falls, injuries, metabolic stress, and further complications of these processes. Therefore, the continuous glucose measure seems to be necessary to take a close look at that problem. In a retrospective review, Drews et al^[68]^ demonstrated that patients with low normal blood glucose, defined as 70 to 89 mg/mL, were at greater risk of developing perioperative hypoglycemia than hyperglycemic patients being treated with insulin; however, hyperglycemic insulin-treated patients were more likely to experience severe hypoglycemia. This evidences the priority of detailed control of glycemia throughout the patients in orthopedic units.

Previously undiagnosed diabetes or so-called hospital-induced stress hyperglycemia carries the same poor prognosis as known DM and should be treated.^[69]^ It is also important to establish a stable regimen of diet and pharmacologic therapy well in advance of anticipated discharge.^[72]^ Patients should be taught basic survival skills by the diabetes educator or nursing staff, particularly if they are new to glucose self-monitoring and insulin administration. Arrangements should be made for an office visit with the primary care physician within 2 weeks of discharge to review and adjust the treatment plan if necessary.

Adequate diabetes management during orthopedic surgery requires close attention to several factors: duration of diabetes, degree of glycemic control, presence and extent of complications, outpatient treatment regimen, and type of surgical procedure. In addition, unique patient situations demand individualization and flexibility of care. Poor acute phase perioperative glycemic control is associated with poor outcome. But the mechanism facilitating the effects are different among diabetic and nondiabetic patients, suggesting different glycemic management strategies for the 2 patient groups and underlying the need for detailed analysis of each patient.^[12]^ Therefore, the proper glycemic control reduces the occurrence of adverse outcomes during the perioperative period. Both hypoglycemia and hyperglycemia can prove to be detrimental and should be avoided by paying close attention to nutritional changes and to the antidiabetic treatment regimen, and by adhering to the general principles outlined above. A culture of optimal management fostered through awareness and education at all levels of surgical care in the hospital setting is vital to achieving and maintaining these objectives.

Results of the presenting paper will allow us to investigate the influence of orthopedic surgery on glycemia and possible modifications of hyperglycemia treatment in perioperative period in patients with T2DM or glucose intolerance. What is more, it will allow for investigation of changes of glycemia in patients with normal glycemia metabolism, potentially protecting them from hypoglycemia during hospital stay and increasing their awareness of potential development of DM in the future. Additionally, this study will correlate perioperative glycemic levels with risk of cardiovascular events in 1-year follow-up, and its influence on SSI and implant complications. Thanks to these findings surgeons will be able to lower the risk of such complications in the future, hence lowering mortality and increase the quality of life, especially in patients with DM and in those with high risk for developing this disorder. Another advantage of this study is the fact that it contains patients without recognized DM and without carbohydrate metabolism disorders and assesses their glycemia fluctuations. Such knowledge might help in development of an algorithm for perioperative care with stress on glucose level control as it is a period when patients are exposed to significant glycemia fluctuations. What is more, it must be emphasized that this study has a unique model, in which glycemia monitoring will involve both pre- and postoperative period for every included patient. Such a way of analyzing patients allows one to form a well visualizing control group, because every measurement after the surgery has its counterpart before the surgery. However this study did not exclude the disadvantages. Patients before the surgery and after hospital discharge will not be monitored all the time. Therefore, we must take into consideration the possible patients’ interference with glycemia levels in opposition to recommendations. That may lead to obtaining invalid results and risk of bias.

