## 2. Materials and Methods

Patients for this prospective observational study will be recruited among those qualified for elective TKA or THA at the Department of Orthopaedics and Rehabilitation in academic Miedzyleski Specialist Hospital in Warsaw. 100 patients will be included. Every patient will be evaluated with the use of Finnish Diabetes Risk Score (FINDRISC), which allows for evaluation of risk of developing DM in 10 year time in patients who were not previously diagnosed^[25–27]^ and SCORE scale, which allows for evaluation of risk of death in 10 years due to cardiovascular events.^[28–31]^ To perform this evaluation data such as sex, age, body mass index (kg/m^2^), and waist circumference (cm) will be measured. Also, data such as physical activity, diet, used medications, smoking, and family history will be collected. Prior to the surgery every patient will undergo a blood withdrawal, which is routinely performed for every patient qualified for the orthopedic surgery. This blood sample analysis will include glycemia level, HbA1c, morphology, renal function parameters, lipidogram, level of C-reactive protein, and urine test. What is more, every patient will fulfill a questionnaire regarding functioning of the joint affected by OA. The scales used will be The Knee injury and Osteoarthritis Outcome Score scale (Knee injury and Osteoarthritis Outcome Score)^[32]^ or Harris Hip Score (HHS) scale^[33]^ according to the affected joint. Both scales contain questions about patients’ everyday life and limb function.

Inclusion criteria consist of willingness to participate in the study, being qualified for TKA or THA due to the primary OA and age >18 years.

Exclusion criteria consist of lack of acceptance to participate in the study, being qualified for nonsurgical treatment, other diseases but DM, compensated thyroid disorders and hypertension, poorly controlled DM and/or poorly controlled hypertension, patients with diabetes mellitus type 1, patients from the rest homes, pregnant women, patients who underwent lower limb surgeries recently, patients who in opinion of the research team might be poorly compliant, poor Polish language fluency.

Patients will have a glycemia measuring device (Dexcom G5, Inc., San Diego, CA) implemented twice. First time 14 days prior to the surgery, second time after the surgery and will keep wearing it for 14 days.

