All patients will undergo TKA and THA procedures with standard perioperative antibiotics prophylaxis with use of 3 doses of 750 mg of cefuroxime–preoperatively, 6 and 12 hours postoperatively, and standard thrombosis prophylaxis of one dose of 40 mg low-molecular weight heparin. In every case posterior-stabilized total knee prosthesis (PERSONA, Zimmer Biomet, Warsaw, IN) or long-stem cementless Polarstem R3 total hip prosthesis (Smith & Nephew, Baar, Switzerland) will be used. Every participant will be rehabilitated immediately after the surgery with full weight bearing walking in the first 24 hours postoperatively, with the discharge from the hospital on the third day postoperatively.

During standard control visit, 14 days after the surgery skin sutures will be removed and the glycemia measuring device will be taken out. The measurements from the whole period of treatment will be collected from the device. Patients will be controlled during the planned visits 3, 6, 12, and 24 months after the surgery. In case of hyperglycemic event at any time of hospital stay or follow-up, patients will be referred to the internal medicine unit and remain controlled by the physicians according to the glycemic control guidelines.

During every visit glycemia level will be measured from standard blood samples, objective functional outcome will be assessed and radiological standard imaging of the operated limb will be performed. History of any cardiovascular event and/or surgical SSI will be noted.

The presenting study meets STrengthening the Reporting of OBservational studies in Epidemiology guidelines for ensuring high-quality presentation of the conducted prospective observational study.

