## 4. Outcomes measure

### 4.1. Primary outcomes

Changes of glycemia levels during 4-week perioperative period: mean glucose level during pre- and postoperative period, 24-hour glucose level amplitude, time of both higher and lower glucose level than average for the day in total, number of periods of both higher and lower than average glycemia levels for the day and its’ duration, number of days with higher mean glucose level than the mean for the corresponding pre- and postoperative period;Any cardiovascular events during follow-up (heart stroke, brain stroke, coronary arteries disease, transient ischemic attack;Any surgical site and/or implant complications during follow-up.

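### Postoperative glucose (days 0 to 14) and complications are counted over the same days, so part of any association read as glucose's influence could run from an early complication to glucose

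*Protocol article*

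**What the plan says.** **Glucose.** The first primary outcome (section 4.1) is "Changes of glycemia levels during 4-week perioperative period". Section 2 has a sensor worn for 14 days before surgery and again, "second time after the surgery and will keep wearing it for 14 days". It comes off at the day-14 visit: "During standard control visit, 14 days after the surgery skin sutures will be removed and the glycemia measuring device will be taken out".

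**Complications.** The other two primary outcomes (section 4.1) are "Any cardiovascular events during follow-up" and "Any surgical site and/or implant complications during follow-up". Neither has a start later than surgery. On recording, section 2 says: "History of any cardiovascular event and/or surgical SSI will be noted". It does not mention an onset date.

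**How the two are linked.** The sample size (section 3) is framed as a comparison of means between patients with and without complications, with a standardised effect of 0.6. The Discussion (section 6) says perioperative glucose will be correlated with cardiovascular events, and then speaks of "its influence on SSI and implant complications". It goes on to say that the findings will help surgeons reduce these complications. The Abstract repeats the influence wording.

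**What is said about bias.** The Discussion names patients' own interference with their glucose while unmonitored. It does not mention that a complication might change glucose.

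**The concern.** For glucose to be read as influencing complications, it has to be measured before them. The preoperative sensor period meets this condition. The postoperative period does not for any complication that starts by day 14, because the days after onset still count towards that patient's postoperative mean, amplitude and time above average.

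The document itself recognises stress-related hyperglycaemia in hospital (Introduction and Discussion). That a wound infection or cardiac event raises glucose by a similar route is an assumption here and is not stated in the text, but it is a plausible one.

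The within-patient design does not protect against this. Subtracting an unaffected preoperative value from an inflated postoperative value leaves the whole inflation in the change score. At stake is the final inference: an association produced partly by early complications would not show that controlling glucose prevents them.

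**Working it through.** **1. The planned effect.** Inputs from section 3: effect size 0.6, two-sided alpha 0.05, power 0.8 (printed as beta), 1:1 allocation, 10% dropout.
- Two-sample t test: 44.59, so 45 per group and 90 in total. This matches the plan.
- Normal approximation: 2 × (1.960 + 0.842)² / 0.6² = 43.6, so 44 per group and 88 in total.
- Dropout: 90 / 0.90 = 100. This matches the plan.

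The arithmetic is sound, so 0.6 SD is the right yardstick for a bias in this contrast.

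**2. The overlap.** Glucose record: 14 + 14 = 28 days. Days that are also outcome time: 0 to 14 after surgery. This is all of the postoperative record and 14/28 = half of the whole.

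**3. Size of a spurious difference.** Neither of the following inputs is in the document, so both are assumptions shown over a range:
- f = share of complications that start in days 0 to 14, with onset spread evenly over that period;
- d = rise in glucose after onset, in between-patient SDs of the 14-day mean.

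With even onset, half of the window lies after onset on average. If glucose has no true effect, the complication group's 14-day postoperative mean is inflated by f × d × 1/2:

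| f | d = 0.5 | d = 1 | d = 2 |
|---|---|---|---|
| 10% | 0.025 | 0.05 | 0.10 |
| 25% | 0.0625 | 0.125 | 0.25 |
| 50% | 0.125 | 0.25 | 0.50 |

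The same calculation in mg/dL, with a rise of 30, an SD of 20 and onset at day 7 (all assumed): with half early, 0.5 × 30 × 7/14 = 7.5 mg/dL, and 7.5/20 = 0.375 SD. With a quarter early, 3.75 mg/dL and 0.19 SD.

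**4. False-positive rate.** Simulation with N = 90, no true effect, a t test of complication versus no complication at 5%, and 3,000 runs per setting. The numbers of complications are also assumed; 45 is the plan's 1:1 split.

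| Complications | f = 25%, d = 1 | f = 50%, d = 1 | f = 50%, d = 2 |
|---|---|---|---|
| 5 | 6.3% | 9.5% | 22.5% |
| 10 | 8.1% | 11.8% | 31.8% |
| 45 | 9.1% | 22.0% | 56.4% |

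When patients with an early complication were left out (landmark at day 14), the mean difference lay between -0.009 and 0.006 SD and the rejection rate between 4.5% and 5.7%.

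**5. Which complications matter.** The Discussion quotes a major cardiac complication rate of 0.2% to 0.8%. In 100 patients that is 100 × 0.002 = 0.2 to 100 × 0.008 = 0.8 expected events. The chance of none is 0.998^100 = 82% to 0.992^100 = 45%. The cardiovascular outcome in section 4.1 is broader than this, but on the document's own figure the practical concern is mainly early infection. No infection rate for this population is given.

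**The case against.** The strongest reply is that the article fixes no analysis that could carry this bias. Section 4.1 lists glucose and complications as separate outcomes and labels none as exposure. Section 3 describes only paired tests of continuous variables. Time-ordering rules are the kind of detail an article leaves to an analysis plan. The full sentence in the Discussion uses the verb correlate, and section 3 reminds the reader that the data are observational. The day-14 visit coincides with sensor removal, so early and late events could be told apart from the visit record.

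Much of this stands, and it rules out several stronger readings that a reader might infer:
- *That the plan counts early complications as explained by glucose.* No written model does so.
- *That the exposure is postoperative glucose.* The text says perioperative, and half of that record is preoperative and cannot be reversed in this way.
- *That the bias has a known size, such as 0.2 to 0.4 SD.* Those values follow only from assumed inputs. With few early complications the bias is trivial.
- *That preoperative glucose must be the main exposure.* The Introduction gives postoperative variability and hypoglycaemia as motivation, so this would change the question.

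The reply does not remove the point. The article itself sets the overlapping windows, sizes the study on patients with versus without complications, and draws a preventive conclusion. Silence on time order would be no finding; overlapping windows joined to that conclusion are.

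**Conclusion.** The point holds in a limited form. If postoperative or change-in-glucose metrics are related to all complications in follow-up, as the text allows, part of the association can run from an early complication to glucose. The preventive conclusion in the Discussion would then not follow. Preoperative metrics, and complications that start after day 14, are unaffected.

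The size cannot be fixed from the document. It is about 0.03 to 0.5 SD against the planned 0.6, assuming that 10% to 50% of complications start by day 14 and that glucose rises by 0.5 to 2 SD after onset. Follow-up runs to 24 months, so the lower end is possible. The documents do not support a claim that the association is mostly or wholly reversed. This should be corrected before analysis; it does not call the design or the sample size into question.

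**What to change.** 1. When relating postoperative or change-in-glucose metrics to complications, count only complications that start after sensor removal at day 14.
2. As a supportive analysis, keep early complications but use only the glucose recorded before onset.
3. Alongside these, relate preoperative glucose (sensor metrics and HbA1c, both already collected) to all complications.
4. Record the onset date of each complication, not only that it occurred. A complication that began before day 14 but was recognised later would otherwise be placed on the wrong side of the landmark.
5. In the Discussion and the Abstract, replace the influence wording with association. Withdraw the claim that the findings will lower risk, and add reverse direction to the stated limitations.

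**Cost.** One added item in the event record, to be collected prospectively because it may not be recoverable later, plus changes of wording. No change to visits or sample size. The real downside is precision: early complications drop out of the landmark analysis, which will have few events to begin with. They remain in the preoperative analysis.
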